## Abstract

The illicit tobacco trade undermines the effectiveness of tobacco tax policies; increases the availability of cheap cigarettes, which, in turn, increases tobacco use and tobacco related deaths; and causes huge revenue losses to governments. There is limited evidence on the extent of illicit tobacco trade particularly cigarettes in Bangladesh. The paper presents the protocol for a mixed-methods study to estimate the extent of illicit cigarette trade in Bangladesh. The study will address three research questions: (a) What proportion of cigarettes sold as retail are illicit? (b) What are the common types of tax avoidance and tax evasion? (c) Can pack examination from the trash recycle market be considered as a new method to assess illicit trade in comparison to that from retailers and streets? Following an observational research method, data will be collected utilizing empty cigarette packs from three sources: (a) retailers; (b) streets; and (c) trash recycle market. In addition, a structured questionnaire will be used to collect information from retailers selling cigarettes. We will select post codes as Primary Sampling Unit (PSU) using a multi-stage random sampling technique. We will randomly select eight districts from eight divisions stratified by those with land border and non-land border; and within each district, we will randomly select ten postcodes, stratified by rural (five) and urban (five) PSU to ensure maximum geographical variation, leading to a total of eighty post codes from eight districts. The analysis will report the proportions of packs that do not comply with the study definition of illicit. Independent estimates of illicit tobacco are rare in low- and middle-income countries such as Bangladesh. Findings will inform efforts by revenue authorities and others to address the effects of illicit trade and counter tobacco industry claims.

## 1. Introduction

The World Health Organization’s (WHO) Framework Convention on Tobacco Control (FCTC) suggests a number of measures to reduce the demand for and supply of tobacco. Elimination of all forms of illicit tobacco trade (Article 15) is an essential tobacco control measure [1,2]. Illicit trade may include large- and small-scale smuggling, illicit manufacturing, and counterfeiting of existing brands [1]. Cigarettes are a particularly attractive product to smugglers [2]. As cigarettes in Low- and Middle-Income Counties (LMICs) have relatively higher taxes compared to other tobacco products such as birris and smokeless tobacco [3], evading tax by diverting cigarettes into the illicit market (where sales are largely tax-free) can generate a considerable profit margin for smugglers [2,4]. Illicit trade undermines the effectiveness of tobacco tax policies, results in availability of cheap cigarettes to smokers, and thus increases tobacco use and tobacco related deaths [2,3]. Elimination or curbing illicit trade will therefore increase price and tax revenue to governments and reduce tobacco consumption and tobacco-related premature deaths [3,5].

The share of illicit in total cigarette consumption is estimated to be 11.6% globally and 16.8% in LMICs [2]. Tobacco companies claim that illicit trade in cigarettes has been growing rapidly since the 1990s [4], and often use inflated estimates of illicit cigarettes to argue against cigarette tax increases [5,6,7,8]. In the absence of national-level independent data on the extent of illicit cigarette trade and limited data on cigarette confiscation provided by the enforcement authorities [3,9], tobacco companies manipulate evidence to their advantage and use these tactics to continually lobby governments for reducing cigarette taxes [3,6,7].

In Bangladesh, 35.3% of adults (38 million) use tobacco regularly, 14% (15 million) use cigarette, and 5% (5.3 million) use “birri” [10]. However, there has been no independent published evidence measuring the extent of illicit tobacco trade in Bangladesh. Nevertheless, following industry estimates, it has been claimed that the illicit cigarette trade would be about 2% of the total cigarette market, leading to a revenue loss of 8 billion Taka, 4% of the total tobacco revenue [11]. 

This protocol will present a mixed-methods study to estimate the extent of illicit cigarette trade in Bangladesh. Three research questions will be addressed: (a) What proportion of cigarettes sold as retail in Bangladesh are illicit? (b) What are the common types of tax avoidance and tax evasion in Bangladesh? (c) Can pack examination from trash recycle market be considered as a new method to assess illicit trade in comparison to that from retailers and streets? Findings from this study will help policy makers develop more effective tobacco control measures and refute industry claims in Bangladesh. 

## 2. Materials and Methods 

Measuring illicit tobacco trade is a complex task due to the illegal nature of the activities involved [2]. Various methods have been used to assess the extent of illicit trade, such as measuring the difference between consumption and tax paid sales, interviewing smokers, studying features of cigarette packs and econometric modeling, each having their own strengths and weaknesses [3,4,12,13]. We will use observational methods and collect data from empty cigarette packs from three sources: (a) from the retailers resulting from their loose cigarette sale [3,14]; (b) littered packs from the streets surrounding the retailers [3,15,16]; and (c) littered packs from trash recycle market. The last one can be considered as an innovation in the methodology for not being applied before and could be particularly useful in LMICs where trash recycle markets are established. Regardless of the pack source, such observational studies provide a direct way to assess illicit trade [7,17].

Once collected, we will examine certain characteristics of cigarette packs such as “no mention of retail price”, “mention of brand element”, “no graphic and textual health warnings”, “no declaration”, “a duty-free sign”, and “absence of correct and authentic tax stamps” of cigarette packs as indicators of being illicit [12]. Such information could also be collected either directly from tobacco users and/or by inspecting tobacco users’ packs. However, as “loose selling” of cigarettes is common and permitted by law in Bangladesh, consumer surveys and pack inspections are of limited use. On the other hand, loose selling makes retailer pack collections more relevant. We will therefore adopt the approach developed by John and Ross (2018) [3] to measure the extent of illicit cigarette sold as retail in Bangladesh. In addition, a structured questionnaire will be used to collect information from retailers selling cigarettes.

### 2.1. Study Sites and Sampling Design

Bangladesh is divided into eight administrative divisions (highest administrative unit) and 64 districts. Bangladesh also has large international land borders with neighboring countries, and therefore 31 districts in six divisions border with India and Myanmar (Table 1). In Appendix A, Figure A1 presents the map of Bangladesh where the green colored places represent the two divisions with no land border area and the rest share land borders with neighboring countries. 

We will use post codes as the primary sampling unit (PSU) and select PSUs using a multi-stage random sampling technique [14]. In a division having districts with borders, we will only consider those districts having borders for inclusion in the study, and randomly select one such district from the division. For instance, while considering Rajshahi division, among eight districts, four (namely, Naogaon, Rajshahi, Nwabganj, and Joypurhat) have areas with a land border. Therefore, the sampling frame would consist of those four districts only and one will be randomly selected. In two divisions, Dhaka and Barisal—where there is no district with international land border—we will randomly select one district from each. For example, in Barishal division, there are six districts (namely, Bhola, Barishal, Barguna, Pirojpur, Patuakhali, and Jhalokathi) and none of them have international border, hence all of them would be considered in the sampling frame for the purpose of random selection. Hence, eight districts will be selected, one from each division. 

Within a district, we will select 10 post codes randomly, 60 post codes from border and 20 from non-boarder districts—a total of 80 post codes from eight districts. The PSUs in each district will also be stratified by rural (five post codes) and urban (five post codes) to ensure maximum geographical variation. Post codes (PSUs) under city corporation or paurasava (municipality) will be defined as “urban” while postcodes outside of those places will be considered as rural. Currently, there are 1216 post codes, each with an average area of 121 square kilometers. The list of the post codes is available by districts and sub districts [18]. Table 2 illustrates the sampling design. 

We will collect the list of districts for each specific division and organize them with respect to their border status. A two-digit serial number would be assigned for each district and following randomization the respective one will be finally selected. Figure A2 in Appendix A presents the selected districts in each division covering urban–rural feature and border–non-border status from where cigarette packs would be collected. 

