In general, all pack characteristics considered for detecting legitimacy in the retailer sample might also be accepted for those in littered or trash samples. Nevertheless, one of the limitations of the above general approach is that it might fail to distinguish between tax evasion and avoidance. More specifically, there may be some legally purchased duty-free packs as well as those bought from neighboring countries, in a sample from street, while also having illegally purchased and illegally sold packs in the retail shops belonging to that street. This possibility might result in under- or overestimation of the illicit cigarette trade. Hence, it rationalizes the application of an adjustment factor while measuring the magnitude of illicit cigarette in the sample collected particularly from street and trash recycle market. Table 3 exemplifies a thematic presentation of legitimacy criterion of a cigarette pack and adjustment requirement in the estimation. 

Assuming that the littered packs in the streets would by and large reflect the average characteristics of those sold by different retailers on the same street, the following adjustment method would be applied:

Suppose DF_L_ is the proportion of duty-free packs (both legal and illegal) in the littered sample and DF_R_ is the proportion of duty-free packs (all illegal) in retailer sample. Then, the estimated proportion of illegal duty-free packs from littered sample would be
=DF_R_ if DF_L_ > DF_R_; and
=DF_L_ if DF_L_ ≤ DF_R_.   

Similar adjustment process would be followed while estimating extent of illicit cigarette using packs from trash recycle sample. It should be noted here that self-made cigarette using tax-paid tobacco powder or crushed tobacco may not be the scope of current work. However, a pack for a local category of cheap cigarette known as “birri” would be collected and examined for its compliance as per the study definition. Statistical Analysis (STATA) software version 15 would be used. The main statistical analysis will report the frequencies and proportions of cigarette packs that do not comply with the tobacco control laws and falls within the study definition of illicit. 

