Another important potential limitation of the proposed methodology would be its ability of correct estimation for the size of illicit market. Since the unit of observation from where packs would be collected is retail cigarette shops, selection bias might remain present in the estimation. The estimate would be overestimated if pack collection takes place in an area where illegal tobacco products are known to be traded. In contrast, the estimates would be underestimated if retailers purposefully preserve the licit cigarette packs in the collection bag. Moreover, conditioning that illicit cigarettes are sold in full packs in general rather than single sticks, collecting empty packs from retailers might underestimate the magnitude. Considering all these potential threats, we expect the study would be free from selection bias as the retailer selection would be completely random covering the urban–rural and border–non-border perspective around the country. The validity and representativeness of the estimate measured using the packs collected from retailers would be ensured by comparing that with the estimate retrieved from littered packs from the streets and packs collected from the trash recycle market in the same neighborhood. Estimates from the two later sources to a greater extent would address the limitations if retailer deposit only licit packs or illegal cigarette happens to be sold in full pack. The comparison of results and further analysis of illicit packs from these three sources would help us to examine the existence of any systematic difference among them. Absence of systematic difference would ensure the possible unbiasedness of the estimates [12].

Finally, in the absence of any prevalence data at the division or district level, it would not be possible to propose a sample size weighted on the local smoking prevalence or smoking intensity. Bangladesh has completed two rounds of Global Adult Tobacco Survey (GATS). However, the first round does not have district level or divisional level information on smoking prevalence while the data from second round have not been released yet. 

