**Stage - Three (Sub - District)**									
5 UPCs form Each District Covering City Corporation/Metropolitan Area/Municipality Area (Paurasava)	UPC - 1	UPC - 1	UPC - 1	UPC - 1	UPC - 1	UPC - 1	UPC - 1	UPC - 1	**Urban Post Codes (UPC):** In each district UPC would be those areas (Sub - Districts) covering Metropolitan Cities or City Corporation Areas or Municipality Area (Paurasava) **Selection Method:** Simple Random Sampling
	UPC - 2	UPC - 2	UPC - 2	UPC - 2	UPC - 2	UPC - 2	UPC - 2	UPC - 2	
	UPC - 3	UPC - 3	UPC - 3	UPC - 3	UPC - 3	UPC - 3	UPC - 3	UPC - 3	
	UPC - 4	UPC - 4	UPC - 4	UPC - 4	UPC - 4	UPC - 4	UPC - 4	UPC - 4	
	UPC - 5	UPC - 5	UPC - 5	UPC - 5	UPC - 5	UPC - 5	UPC - 5	UPC - 5	
5 RPCs/BPCs form Each District Situated in different Sub Districts (Outside City Corporation/ Metropolitan Area/Municipality Area)	RPC - 1	RPC - 1	BPC - 1	BPC - 1	BPC - 1	BPC - 1	BPC - 1	BPC - 1	**Rural Post Codes/Border Area Post Codes (RPC/BPC):** **No Land Border Area:** RPC would be those areas (Sub - Districts) covering outside Metropolitan Cities or City Corporation Areas or Municipality areas (Paurasava). **Have Land Border Area:** BPC would be those areas (Sub - Districts) covering outside Metropolitan City or City Corporation Areas Municipality areas (Paurasava) as well as sharing land border. **Selection Method:** Simple Random Sampling
	RPC - 2	RPC - 2	BPC - 2	BPC - 2	BPC - 2	BPC - 2	BPC - 2	BPC - 2	
	RPC - 3	RPC - 3	BPC - 3	BPC - 3	BPC - 3	BPC - 3	BPC - 3	BPC - 3	
	RPC - 4	RPC - 4	BPC - 4	BPC - 4	BPC - 4	BPC - 4	BPC - 4	BPC - 4	
	RPC - 5	RPC - 5	BPC - 5	BPC - 5	BPC - 5	BPC - 5	BPC - 5	BPC - 5	

**Table 3 ijerph-17-04791-t003:** Legitimacy Criterion of Cigarette Pack and Bias Correction.

Pack Source	Tax Status	Packaging Compliance	Legitimacy of Cigarette Pack	Bias Correction in Estimate
**Retailers**	Paid	Compliant	Legal	No Adjustment Required
		Not Complaint	Illegal	
	Not Paid	Compliant	Illegal	
		Not Complaint	Illegal	
**Streets/Trash Recycle Market**	Paid	Compliant	Legal	No Adjustment Required
		Not Complaint	Might be Legal or Illegal	Adjustment Applied
	Not Paid	Compliant	Might be Legal or Illegal	
		Not Complaint	Might be Legal or Illegal

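### The sampling frame leaves out 14 of 64 districts and leans to the border, so it cannot support the Bangladesh-wide estimate that the protocol claims

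*Protocol article*

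**What the plan says.** Research question (a) in section 1 is national: "What proportion of cigarettes sold as retail in Bangladesh are illicit". Section 5 repeats that aim and presents country-wide coverage of border and non-border areas as a strength. Section 4 expects no selection bias, on the ground that retailers are chosen at random.

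Section 2.1 notes that "31 districts in six divisions border with India and Myanmar" and then restricts the frame: "In a division having districts with borders, we will only consider those districts having borders for inclusion in the study". One eligible district is then drawn at random in each such division. Dhaka and Barishal have no border districts, so there the draw is from all districts. Each of the eight chosen districts gives ten post codes, five urban and five rural.

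On the rural stratum, section 2.1 says of city corporations and municipalities that "postcodes outside of those places will be considered as rural". Table 2 (stage three) adds a condition in the border districts: the non-urban areas must lie outside "Metropolitan City or City Corporation Areas Municipality areas (Paurasava) as well as sharing land border".

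Section 3 states: "The main statistical analysis will report the frequencies and proportions of cigarette packs", with each pack source analysed separately. It mentions no selection weights. The only remark on weighting, in section 4, is about allocating sample size by smoking prevalence, which is a different matter.

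**The concern.** A probability sample supports a national figure only if every unit has a known, non-zero chance of selection. Here some districts have none, and the limitations in section 4 do not say so.

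The sample is also tilted towards the border by design. No division supplies both border and non-border districts, so border status cannot be separated from division. A simple proportion across sites would be a border-heavy average.

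The stakes are practical. Section 1 cites an industry-derived figure of about 2% of the market, and the study is meant to counter industry claims. At that level, a shift of one or two percentage points changes the message.

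**Working it through.** **Inputs from Table 1 (border / non-border districts).** Sylhet 4/0, Rangpur 6/2, Rajshahi 4/4, Mymensingh 4/0, Khulna 6/4, Chittagong 7/4, Dhaka 0/13, Barishal 0/6.

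**Reproducing the protocol's figures.**
- Border districts: 4 + 6 + 4 + 4 + 6 + 7 = 31.
- Non-border districts: 14 + 13 + 6 = 33. Total 64, as stated.
- Post codes: 6 × 10 = 60 border and 2 × 10 = 20 non-border, total 80, as stated.

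**Coverage.**
- Excluded: Rangpur 2 + Rajshahi 4 + Khulna 4 + Chittagong 4 = 14. Sylhet and Mymensingh lose none.
- 14/64 = 21.9% of all districts; 14/33 = 42.4% of non-border districts.
- Eligible frame: 64 − 14 = 50 districts (31 border, 19 non-border).
- All non-border data come from one district of 13 in Dhaka and one of 6 in Barishal.

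**Composition.** Border share of post codes is 60/80 = 75%; border share of districts is 31/64 = 48.4%.

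**District-stage weights.** The weight is the number of eligible districts in the division, since one is drawn. It runs from 4 (Sylhet, Rajshahi, Mymensingh) to 13 (Dhaka), a ratio of 13/4 = 3.25.

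**Rural stratum.** If Table 2 governs, 6 × 5 = 30 of the 40 rural post codes must come from areas sharing the land border. If section 2.1 governs, no such condition applies. These are different samples.

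**Illustration.** The protocol gives no border rate (pb) or non-border rate (pn), so these are assumed, with equal packs per post code and equal weight per district:
- simple proportion: 0.75 pb + 0.25 pn
- district weights on the eligible frame: (31 pb + 19 pn)/50
- all districts: (31 pb + 33 pn)/64

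| pb, pn | Simple | 50-district frame | All 64 districts |
|---|---|---|---|
| 2%, 2% | 2.0% | 2.0% | 2.0% |
| 4%, 2% | 3.5% | 3.2% | 3.0% |
| 6%, 2% | 5.0% | 4.5% | 3.9% |
| 10%, 2% | 8.0% | 7.0% | 5.9% |

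In the last row the gap has two parts. Moving from 8.0% to 7.0% is a matter of weighting and can be repaired in the analysis. Moving from 7.0% to 5.9% is a matter of coverage. Weights cannot repair it, unless one assumes that Dhaka and Barishal stand in for the excluded districts.

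**The case against.** The border emphasis is deliberate and openly stated, and oversampling a stratum of interest is legitimate. Survey weights are commonly left to an analysis plan that is not shown here. Packs from streets and trash markets offer a cross-check.

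Much of this stands, and it limits what can be said:
- A reader might infer that the protocol commits to unweighted pooling. It does not. It promises frequencies and proportions and is silent on weights.
- A reader might infer that all six border divisions lose districts. Only four do.
- A reader might infer that each rural post code must itself touch the border. Table 2 defines these areas at sub-district level, so the condition may apply to the sub-district.
- A reader might take 75% as the border share of packs. It is the share of post codes; pack yield per post code is unknown.
- A reader might infer that upward bias is established, because section 4 says "The estimate would be overestimated if pack collection takes place in an area where illegal tobacco products are known to be traded". That sentence does not call border districts such areas. Upward bias is plausible, not shown.

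None of this rescues the national claim. Oversampling needs a non-zero chance everywhere, and no analysis plan can weight a district that cannot be drawn. The street and trash packs come from the same neighbourhoods as the retailers, so agreement between the sources cannot reveal the gap.

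**Conclusion.** The point holds as a mismatch between the claim and the frame. With 14 of 64 districts at zero selection probability, the study can describe the border districts of six divisions plus Dhaka and Barishal divisions, but not Bangladesh. Nor can it expect to be without selection bias at national level. The contradiction between section 2.1 and Table 2 on rural eligibility is a separate fact of the text.

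These conclusions rest on the protocol's own counts. The size of any bias does not: the 8.0%, 7.0% and 5.9% depend on assumed rates, equal packs per post code and equal weight per district, and the bias is zero if border and non-border rates are equal.

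**What to change.** 1. Restate the target population as the border districts of six divisions plus Dhaka and Barishal divisions. Drop the national wording and the expectation of no selection bias, and list the excluded districts as a limitation.
2. Make separate border and non-border estimates the main result for each pack source.
3. Weight any overall figure by inverse selection probability: (eligible districts in the division) × (eligible post codes in the urban or rural stratum / 5). Label it as applying to the sampled frame only.
4. Reconcile section 2.1 with Table 2 on which rural post codes are eligible, and use the same definition in the weights. If the border condition is kept, the restated target must carry it too.

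Districts should not be redrawn in only some divisions. Section 2.1 refers to a figure of districts already selected, and a partial redraw would give a mixed frame that fits neither target.

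The cost is a narrower claim and somewhat wider intervals for the weighted total. Section 2.1 says post codes are listed by district and sub-district; classifying them as urban, rural or border may take some further work.

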### 2.2. Data Collection and Management

From each PSU, three methods will be used—collecting packs from: tobacco retailers; those discarded in the street; and those discarded in trash recycle markets. An interview of the same cigarette retailers supplying packs for the study will also be carried out. 

